### **Generalisability**

- Study sites are restricted to specific regions of Portugal and population. Results may not be applicable to overall individuals or settings.

## **8. Safety Reporting and Related Procedures**

### **8.1. Adverse Events and Serious Adverse Events**

An **adverse event (AE)** is generally defined as any unfavorable and unintended diagnosis, symptom, sign (including an abnormal laboratory finding), syndrome or disease which either occurs during the study, having been absent at baseline, or if present at baseline, appears to worsen. Adverse events are to be recording regardless of their relationship to the study intervention.

Changes resulting from normal growth and development that do not vary significantly in frequency or severity from expected levels are not to be considered adverse events. Examples of this may include, but are not limited to, teething, typical crying in infants and children and onset of menses or menopause occurring at a physiologically appropriate time.

A **serious adverse event (SAE)** is generally defined as any untoward medical occurrence that results in death, is life threatening, requires inpatient hospitalization or prolongation of existing hospitalization, results in persistent or significant disability/incapacity, or is a congenital anomaly.

Other important medical events that may not result in death, may not be life-threatening, or may not require hospitalization may be considered a Serious Adverse Event when, based upon appropriate medical judgment, they may jeopardize the patient or subject and may require medical or surgical intervention to prevent one of the other outcomes listed previously. Examples of such medical events include allergic bronchospasm requiring intensive treatment in an emergency room or at home and blood dyscrasias or convulsions that do not result in inpatient hospitalization.

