**Table 4 - Overview of data collection schedule and measurements**

| Time points / Data                                    | T0              | Ongoing (only intervention arm) | T1       | T2       |
|-------------------------------------------------------|-----------------|---------------------------------|----------|----------|
|                                                       | Recruitment - 0 | Intervention time span          | 3 months | 6 months |
| Socio-demographic and clinic characterization         | X               |                                 |          |          |
| Self-rated health status (SRH)(94)                    | X               |                                 |          |          |
| PPI specific outcomes                                 | X               |                                 | X        | X        |
| Other medication related outcomes                     | X               |                                 |          | X        |
| Quality of life (EQ-5D-5L)(90,91)                     | X               |                                 |          | X        |
| BMQ specific(92) applied to PPI                       | X               |                                 | X        |          |
| Adherence (MTA)                                       | X               |                                 |          | X        |
| Healthcare resource utilization (Economic Evaluation) | X               |                                 |          | X        |
| Intervention satisfaction questionnaire               |                 |                                 |          | X        |
| Process parameters                                    |                 | X                               |          |          |

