| Emergency room (ER) visits Y/N                                               | 
 
• Yes
 
• No
 
                                                     | Telephone interview                                | T0, T2 |
| Number of Emergency room (ER) visits                                         | 
 
• n emergency room visits
 
                                               | Telephone interview                                | T0, T2 |
| Hospitalizations Y/N                                                         | 
 
• Yes
 
• No
 
                                                     | Telephone interview                                | T0, T2 |

|                                                                                       |                                                                     |                                                 |        |
|---------------------------------------------------------------------------------------|---------------------------------------------------------------------|-------------------------------------------------|--------|
| Hospitalizations - Name of the Hospital                                               | • text                                                              | Telephone interview                             | T0, T2 |
| Number of Hospitalizations (total)                                                    | • n hospitalizations                                                | Telephone interview                             | T0, T2 |
| Number by Type of Hospitalization                                                     | • n hospitalizations unplanned
• n hospitalizations planned      | Telephone interview                             | T0, T2 |
| Major motive for Hospitalization                                                      | • text (e.g. organ/ surgery)                                        | Telephone interview                             | T0, T2 |
| Hospitalization LOS                                                                   | • n (nights)                                                        | Telephone interview                             | T0, T2 |

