#### **Secondary outcomes**

Descriptive statistics will be calculated for all patients and reported with respect to each time point. Adequate GLM models will be used to compare groups with respect to clinic characteristics, therapeutic outcomes (PPI specific and other medication), Quality of life (EQ-5D-5L), BMQ specific applied to PPI, Adherence (MTA) and healthcare resource utilization. Changes over time points will be evaluated.

Patients' level of satisfaction and process outcomes will be analyzed only for the intervention arm. Process outcomes will be used to assess the fidelity and quality of the collaborative intervention.

Time to PPI discontinuation will be accessed through Kaplan-Meier (KM) estimator. Results will be stratified by group and KM curves will be presented. Log-rank test will be computed to compare results between cohort subgroups. If groups are unbalanced with respect to potential confounders, multivariate Cox Proportional Hazards models will be used instead. Univariate and multivariate hazard ratios (HR) will be computed, and Wald's 95% CI presented. Patients will be censored in the survival

analysis if they were lost to follow-up (subjects who could not be reached by telephone interview, or the primary outcome could not be computed or withdrew consent), hospitalized or died.

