### **6.17.2. Measurement and valuation of resources**

Health care resource use data will be based on patient-reported data. Data will be collected for the following period: baseline and 6-month follow-up. At baseline, information will cover the previous 6 months; at 6-month follow-up the service use since the previous time-point was recorded (baseline).

Resource-use information will be collected using questionnaires developed by the research team. The following resources, identified on literature (84,101) will be collected: regular medications used, number of doctor's appointments by type and setting (GP and specialist, public and private); number of emergency care episodes, number and major motive of hospitalizations, length of stay (LOS), number and type of diagnostic and therapeutic tests related with gastrointestinal symptoms.

For each item of service use reported in the resource use questionnaires, a unit cost will be applied and the total costs for each individual will be calculated. All unit costs will be for the most recent financial year over which the trial data will be collected and will be reported in Euros. Unit costs will be retrieved mostly from Portuguese official sources.

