### **8.2. Adverse Event Reporting**

All AEs that occurred in enrolled patients exposed to the inhaler medication of interest or other concomitant medication, irrespective of seriousness or causality will be reported to the local Health Authority in accordance with national regulatory requirements for individual case safety reporting.

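### Hospital admission and death are both censoring events and serious adverse events, but admissions are asked about only once after enrolment and without a date, and death has no variable or source

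*Protocol*

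**What the plan says.** - **Safety definitions.** Section 8.1 defines a serious adverse event as one that "results in death, is life threatening, requires inpatient hospitalization or prolongation of existing hospitalization", among other criteria, and adds: "Adverse events are to be recording regardless of their relationship to the study intervention". Under section 8.2, adverse events "irrespective of seriousness or causality will be reported to the local Health Authority". Neither section names a collection form or a source for admissions or deaths.
- **Censoring rule.** In section 6.15.2 (Secondary outcomes), patients leave the time-to-discontinuation analysis if they are lost to follow-up, a term explained in brackets, or for either of two further reasons. The list ends "or the primary outcome could not be computed or withdrew consent), hospitalized or died".
- **Admissions data.** Table 4 schedules resource use at T0 and T2, not at 3 months. Table 5 lists, at T0 and T2, whether the patient was admitted, the hospital, the number of admissions, planned or unplanned, the main reason, nights, and intensive-care nights. It has no admission or discharge date.
- **Source.** Section 6.17.2 states: "Health care resource use data will be based on patient-reported data". The T0 question looks back over the 6 months before enrolment. Section 7 (Information bias) rules out clinical and hospital records as infeasible.
- **Death.** Table 5 has no item for vital status or date of death.
- **Discontinuation date.** Table 5 does record when the PPI was stopped, as month and year, at T1 and T2.

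**The concern.** The protocol uses admission and death in two ways: as reasons to censor, and as serious events to be recorded whatever their cause. Both uses need to know that the event happened and when. The data tables treat admission as an economic count recalled at month 6 and do not mention death. What is at stake is whether one secondary analysis can be run as written, and whether serious events are ascertained by a planned route that is the same in both arms. The SAP may settle how to code censoring, but it cannot supply dates that were never collected.

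**Working it through.** **1. Is the censoring rule executable with the listed data?** Take a patient whose recorded discontinuation is in month 2 and who reports one admission at T2.
- Admission in month 1: the patient is censored at month 1 and contributes no event.
- Admission in month 5: the patient is an event at month 2.

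The listed data are identical in both cases, so event status is undetermined as well as time. For an admitted patient who never stopped the PPI, status is clear (censored), but the time could lie anywhere between enrolment and T2.

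**2. Can a death be told apart from loss?** Loss to follow-up is defined as "subjects who could not be reached by telephone interview, or the primary outcome could not be computed or withdrew consent". A patient who has died also cannot be reached by telephone. The dispensing extracts at 3 and 6 months show purchases, not vital status. No listed field separates the two.

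**3. When is an admission first asked about?** T2 may be held 1 month either side of month 6, so at month 5 to 7. Assume admissions are spread evenly over the time up to the T2 call at month T. The mean delay is T/2, and the share delayed by more than 3 months is (T-3)/T.

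| T2 call at month | Mean delay (months) | Longest (months) | Share over 3 months |
|---|---|---|---|
| 5 | 2.5 | 5 | 2/5 = 40% |
| 6 | 3.0 | 6 | 3/6 = 50% |
| 7 | 3.5 | 7 | 4/7 = 57% |

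If the question were also asked at T1, with calls at months 3 and 6, the mean delay would be 3/2 = 1.5 months and the longest 3. At the widest spacing the windows allow (months 2 and 7), the longest would be 7 - 2 = 5 months instead of 7.

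**4. How many patients?** The protocol gives no admission or death rate. The only protocol figures used are its enrolment target and its planning rates. Its 89 per group reproduces (two-sided Fisher test, 10% against 30%: power 0.9017), and 178/0.80 = 222.5, stated as 222. The point does not rest on these.
- Assumed 5% to 15% admitted in 6 months: 222 x 0.05 = 11.1 to 222 x 0.15 = 33.3 patients with an undated admission.
- Assumed 0.5% to 3% dead: 222 x 0.005 = 1.1 to 222 x 0.03 = 6.7 deaths without a source.
- Admitted patients who also discontinue, whose event status is therefore undetermined: with the planning rates of 10% and 30%, and admission assumed independent of discontinuation, 111 x 0.05 x (0.10 + 0.30) = 2.2 to 111 x 0.15 x 0.40 = 6.7. This compares with 111 x 0.40 = 44 discontinuations in all, before losses.

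**The case against.** **Earlier routes exist.** In section 6.5 the intervention-arm pharmacist telephones at 2 weeks, and at 4 weeks where reduction or withdrawal is indicated, and can send an urgent alert about a severe symptom. Section 6.10 has any suspected adverse drug event that becomes known reported to the research team and the national system. This stands in part. A reader might infer that every serious event surfaces months late or that nobody could act on it; the protocol does not support that, since the patient's own GP makes the withdrawal decision and patients may seek advice at any time. But these routes do not ask about admissions or deaths, the alert is optional, and the control arm has no such calls. The scheduled T0 and T2 questions are the same in both arms; the unevenness comes only from the extra intervention-arm contacts.

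**The rule fixes no censoring time.** Section 6.15.2 says who is censored, not when, so the SAP could use last known PPI status. That is workable, but it replaces a rule based on admission with another one and does not establish which came first.

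**Deaths are not defined as dropouts.** A reader might infer that all deaths would be counted as losses. Section 6.15.2 lists death separately, so the authors mean to distinguish it; what is missing is the means. The 20% loss allowance (0.20 x 111 = 22 per arm) is a sample-size figure and says nothing about deaths.

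**The questionnaires are not shown.** Annexes 13 and 14 are separate documents and might ask more. Section 6.12, however, presents Table 5 as the summary of variables, time points and sources, and it lists none of these items.

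**Conclusion.** The point holds in limited form. As listed, the data leave censoring status and time undefined for admitted patients in the time-to-discontinuation analysis, and they give death no source. Under the assumed rates this means about 11-33 undated admissions, of which about 2-7 would leave event status undetermined, and about 1-7 deaths. These ranges rest on assumed rates, even timing of admissions and independence of admission from discontinuation; none of that comes from the protocol. The 6-month primary analysis compares proportions and does not use the censoring rule.

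An earlier question should not be oversold as a safety alarm. With two months of recruitment (8.7 weeks) and GP contact within 2 weeks, withdrawal decisions would be largely made by about week 11, while the first patient's nominal 3-month call falls at week 13 (week 8.7 at the earliest edge of its window). The gain is a rule that can be carried out, and SAE ascertainment that is earlier and equal in both arms.

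**What to change.** - In Tables 4 and 5 and in the 3- and 6-month questionnaires (Annexes 13 and 14), add for both arms at T1 and T2: any admission since the last contact, its date and its reason.
- Add vital status with date of death to Table 5, and name the source: whoever answers a failed call, or the recruiting pharmacy.
- State in section 8.2 that admissions and deaths learned at these calls are entered in the SAE record.

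The calls to both arms already exist, so no new contact is needed. The cost is a few questions, a slightly longer 3-month call and a few table rows.

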### **8.2. Adverse Event Reporting**

All AEs that occurred in enrolled patients exposed to the inhaler medication of interest or other concomitant medication, irrespective of seriousness or causality will be reported to the local Health Authority in accordance with national regulatory requirements for individual case safety reporting.

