Secondly, after patient recruitment, a therapeutic profile will be drawn up and analyzed by the research team to list all medications taken by the patient in a regular basis and identify medication duplications and relevant drug-drug interactions (DDIs) (**Annex 7**). The therapeutic profile will be drafted based in extracted data from the pharmacies software regarding the sales associated to the patients' tax information number (NIF) and confirmed by patient self-report, via a telephone interview with the research team. DDIs will be assessed using Sifarma® software. In this telephone interview, the research team will confirm the use of the listed medications (prescription-only-medicines (POMs) and OTC). Further data for study purposes (e.g PROMs) will also be collected in the telephone interview (**Annex 8**). The final therapeutic profile and related safety information will then be sent to the community pharmacist by email (with access key) to be shared with the patient GP for clinical assessment.

Thirdly, the pharmacist will gather all the information, the PPI deprescribing recommendation and the therapeutic profile with identified moderate and severe DDIs provided by the research team and share with the GP. A specific paper case report form "Passaporte do utente" (**Annex 9**) will be used to exchange information between both pharmacists and GP.

Fourth, The GP with the information provided by the pharmacist and that in his/her medical records, will assess the PPI use and other reported safety issues (DDIs). The patient will be contacted by the GP to discuss the PPI deprescribing pertinence and strategy and, solve other possible medication related problems. All patients will be contacted by the GP preferably by telephone. A face-to-face consultation can be scheduled if the GP considers relevant. Fifth, the PPI withdrawal decision and adopted strategy agreed with the patient will be communicated to the pharmacist using the paper case report. Sixth, after the GP report to pharmacist, of the PPI withdrawal decision, pharmacist will contact the patient by telephone at 2 and 4 weeks, to monitor possible symptoms relapses, answer questions and if applicable, define with the patient a control-symptoms strategy (non-pharmacological) pre-agreed with the GPs under the designed intervention. The 4-week telephone interview will occur only on patients with PPI dose reduction or withdrawal indication. At the end of the withdrawal follow-up

---

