We intend, as part of the intervention, to be the pharmacist to collect all information regarding patients' medication profile. However due to the Covid-19 pandemic, the research team thought to reduce patient-community pharmacist face-to-face interaction time, and withdrawal from the pharmacist intervention package the task not directly related with the main PPIs' deprescribing and educational goals.

period, pharmacist will share the follow-up information with the GP using the established communication model. If any severe symptom is identified during this time span, pharmacists can send an urgent alert email to the FHU research coordinator. To assist the pharmacist through all intervention, a complete intervention log form, which include the telephone interview script (**Annex 10**), will be made available by the research team.

Patients can at any moment seek advice with community pharmacies and/or general practitioners. The overview of the multifaceted collaborative intervention package is depicted in Figure 2. intervention details are accessible on the C-SENIoR Intervention Flowchart (**Annex 11**).

[figure not shown]

**Figure 2** - Overview of the C-SENIoR multifaceted collaborative intervention package

The educational booklet was developed by the research team (pharmacists and general practitioners) for the study purpose. We performed a literature review of resources already tested in deprescribing interventions and available online (e.g., <https://deprescribing.org/>) and followed Fajardo et al recommendations (88) concerning readability of patient education materials for deprescribing interventions. The booklet is being tested with PPI elderly users, regarding its readability, dimension, key messages comprehension and images understanding.

This project will have the assistance of a clinical research associate (CRA) who will guarantee the information change flow foreseen between pharmacies and FHUs in the intervention arm.

Patients recruited from pharmacies assigned to the control group will receive usual care. For both groups, a baseline paper-based questionnaires will be delivered by the pharmacist (Annex 4), and three

telephone interviews, will be conducted by the research team at baseline, 3- and 6-month follow-up, respectively, to collect study data (see table 1).

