#### Change in other Medication-related parameters | Profile and Safety outcomes.

- Medication burden that is, the mean number of regular medications patient take and proportion of patients on polypharmacy (patients with 5 or more medicines as commonly accepted definition (89)), assessed at baseline and 6-month follow-up.
- Drug-drug interactions (DDIs), that is, the absolute and relative counts of drug-drug interactions and by degree of severity, patients with any drug-drug interaction and with severe interactions. Most frequent severe drug-drug combinations will also be reported. Drug-drug interactions will be assessed by sifarma® software interaction alert system considering all medications taken, assessed at baseline and 6-month follow-up. Moderate and serious DDIs will be checked by the researchers using the Sifarma® software safety module. This module is an Electronic Information platform on medicines integrated on the Sifarma® dispense software, with updated information regarding clinically relevant Drug-Drug interactions (DDIs). This platform is powered with the summary of medicine characteristics (RCM) and other information sources as Stokley's Drug Interactions and Lexicomp. DDIs are classified according with 2 types of severity: a) Moderate DDI - Drug associations which benefit from (or for which it is recommended) monitoring, dose adjustment or any other form of management; b) Severe DDI - potential life-threatening and/or requiring medical intervention to minimize or prevent serious adverse effects; drugs are contraindicated for concurrent use. The software

displays an automatic alert regarding the DDIs identified and provide additional information regarding the mechanism of interaction.

- Adverse drug events, that is, the absolute and relative counts of self-reported adverse drug events and type of events (e.g., needed professional support) experienced by patients, assessed at baseline and 6-month follow-up.

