#### **6.10. Potential harms and patient safety**

Because of the pharmacological characteristics of the PPI there is a possibility that the discontinuation might lead to symptoms relapse (e.g., rebound hyperacidity) or complications (95). However, the potential for serious harm due to adverse drug withdrawal events (ADWEs) appears to be rare (96) and several drug class specific deprescribing interventions have found no difference in the rate of ADWEs between control and intervention groups (35). We expect a low probability of relapses or complications as only non-evidenced based medications will be withdrawn and the best evidence deprescribing guidelines will be followed (87). Additionally, patients will have the pharmacist and general practitioner support to help them to manage potential symptomatology with non-drug approaches, use of OTC medicines or, if necessary, to review the PPI dose, indication to use on-demand or full restart of the medication based on the best evidence. Any suspected adverse drug event (ADE) acknowledged will be reported to the study research team and to the National Pharmacovigilance System through "Portal RAM" from the National Authority of Medicines and Health Products, I.P (INFARMED) site.

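### Adverse-event reporting in 8.2 is tied to an inhaler and disagrees with 8.1 and 6.10; symptom relapse is actively monitored in the intervention arm only, so withdrawal symptoms have no like-for-like comparison

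*Protocol*

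**What the plan says.** Three places in the protocol govern adverse events.

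- Section 8.1 defines an adverse event broadly and states: "Adverse events are to be recording regardless of their relationship to the study intervention".
- Section 8.2 sends events to the health authority, whatever their seriousness or cause, for this group: "All AEs that occurred in enrolled patients exposed to the inhaler medication of interest or other concomitant medication".
- Section 6.10 says: "Any suspected adverse drug event (ADE) acknowledged will be reported to the study research team and to the National Pharmacovigilance System".

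Section 6.10 also names the harm to expect: "there is a possibility that the discontinuation might lead to symptoms relapse (e.g., rebound hyperacidity) or complications".

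On follow-up of that harm, section 6.5 says that after the GP has reported the decision, the "pharmacist will contact the patient by telephone at 2 and 4 weeks, to monitor possible symptoms relapses". It then limits the second call: "The 4-week telephone interview will occur only on patients with PPI dose reduction or withdrawal indication". For the other arm it says: "Patients recruited from pharmacies assigned to the control group will receive usual care".

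The safety outcome in section 6.8 is "the absolute and relative counts of self-reported adverse drug events and type of events", taken at baseline and 6 months. Table 5 (section 6.12) lists the matching variables: any adverse drug event, how many, and whether professional support was needed, by telephone at T0 and T2.

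**The concern.** The section headed adverse-event reporting names a product class that this trial does not study. It also conditions reporting on exposure, whereas the risk that the protocol itself describes arises when exposure is reduced or ends. A pharmacist or investigator who reads 8.1, 8.2 and 6.10 together gets three different answers about what must be reported.

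The second part concerns comparison. The rationale in the Protocol Summary expects deprescribing to reduce adverse drug events, and change in those events is a secondary outcome. Harm from taking a drug is thus measured in both arms, while symptoms that return after a drug is stopped are actively sought in one arm only. If self-reported adverse drug events fall in the intervention arm, a report could present that as better safety without any comparable figure for returning symptoms.

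**Working it through.** The point is textual and there is no stated figure to reproduce. The check sets the sections side by side.

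**Step 1: the reporting rules.**

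| Section | Which events | Condition | Events after PPI reduction or withdrawal named in the rule? |
|---|---|---|---|
| 8.1 (record) | all adverse events | none | no, though a returning or worsening symptom fits the definition |
| 8.2 (report to authority) | all adverse events, any seriousness or cause | exposure to an inhaler or other concomitant medication | no |
| 6.10 (report to research team and national system) | suspected adverse drug events that come to notice | none, in either arm | no, though the paragraph discusses them |

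Section 8.2 can be read in two ways.

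- Narrowly, by the named product, it covers nobody.
- Broadly, through its clause on concomitant medication, it covers almost everyone, because each patient enters on a PPI taken for more than 8 weeks (6.3.1). Every adverse event would then go to the authority whatever its cause, which does not match 6.10.

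Neither reading agrees with the other two sections. Section 8.1 also carries examples (teething, crying in infants, onset of menses) that cannot apply to people aged 65 or over, which suggests that section 8 was carried over from other studies.

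**Step 2: where 8.1 would be carried out.** Table 5 has no general adverse-event variable, only the adverse drug event items. The annex list (Table 6) names no adverse-event form.

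**Step 3: what is collected that bears on relapse.**

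| Source | Intervention arm | Control arm | Time | Direct measure of relapse? |
|---|---|---|---|---|
| Pharmacist calls (6.5) | yes; second call for a subset | no | 2 and 4 weeks after the GP report | monitored; Table 5 lists only call date and duration |
| Self-reported adverse drug events | yes | yes | T0, T2 | no |
| Gastric tests, emergency visits, hospitalizations | yes | yes | T0, T2 | no |
| EQ-5D-5L (includes pain/discomfort) | yes | yes | T0, T2 | no |
| PPI use | yes | yes | T0, T1, T2 | no; shows restarting, not symptoms |

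Table 5 marks satisfaction and process items as intervention-only and does not so mark the other rows, so they are read here as collected in both arms.

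**Step 4: timing.** Section 6.5 expects GP contact 1 to 2 weeks after recruitment. If the GP reports at once (an assumption), the last scheduled relapse call falls at 1 + 4 = 5 to 2 + 4 = 6 weeks. T1 is at 3 months, about 3 × 52/12 = 13 weeks, and adverse drug events are not asked then. They are next asked at 6 months.

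**Step 5: how many patients the comparison concerns.** Section 6.11 assumes rates of 10% in controls and 30% under the intervention, with 111 enrolled per arm. That is about 0.10 × 111 = 11 control and 0.30 × 111 = 33 intervention patients who discontinue, before loss to follow-up.

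**The case against.** The strongest reply has four parts.

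1. **Section 8.2 is not the only safeguard.** Section 6.10 reports any suspected adverse drug event in either arm, and 6.5 provides an urgent alert email if a severe symptom appears during withdrawal follow-up. The 8.1 definition covers a returning symptom. This stands. A reader might infer that withdrawal events have no reporting trigger at all, and the documents do not support that. The rule is wrong and conflicts with its neighbours, but partial fallbacks exist.

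2. **Both arms are compared on several related measures.** This also stands. A reader might infer that relapse cannot be seen in the comparison, or that none of the 111 control patients would have relapse data. Neither follows. The measures in Step 3 give an indirect comparison. Table 5 is described as a summary, and Annexes 13 and 14 (the 3- and 6-month questionnaires) are not shown and may contain such an item. The figure of 111 is also the wrong denominator, since relapse after stopping concerns only those who reduce or stop.

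3. **The protocol does not define adverse drug events so as to exclude withdrawal symptoms.** Correct, and the question's wording is in annexes not shown. It follows only that such symptoms may be missed, not that they will be. Nor is it shown that relapse is recorded as data even in the intervention arm: the text says it is monitored, and the Annex 10 log is not shown.

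4. **The calls are part of the intervention under test, and relapse is not a stated objective.** True. Giving the calls to one arm is no contradiction, and a common relapse item is an improvement, not the correction of an error. The improvement is still worth making, because 6.10 cites studies that compared withdrawal events between arms and the protocol text shows no such measure here.

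**Conclusion.** Two separate conclusions hold.

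First, 8.2 is a wrong rule: it names a product not studied, omits events after reduction or withdrawal, and disagrees with 8.1 and 6.10. This rests on the text alone.

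Second, on the protocol text there is no like-for-like comparison of withdrawal symptoms. Active monitoring is described in one arm only and, on the assumption in Step 4, ends about 5 to 6 weeks after recruitment in a 6-month follow-up. The variables common to both arms are indirect. This rests on Table 5 being complete on the point and on Annexes 13 and 14 holding no such item.

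No power figure or primary-outcome estimate is affected. The risk is one of interpretation: fewer self-reported adverse drug events could be reported as a safety gain with nothing comparable on returning symptoms beside it. The direction of any bias is not known, since extra contact in one arm may also raise adverse drug event reporting there. With perhaps 11 control and 33 intervention patients expected to discontinue, the added item would support description by arm rather than a powered test. The change should be made, and it is inexpensive.

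**What to change.** - **Section 8.2:** replace the inhaler wording with text covering enrolled patients in either arm, and state that events after PPI dose reduction or withdrawal are included.
- **Reconcile 8.1, 8.2, 6.10 and Table 5:** make them agree on which events are recorded, which are reported and to whom, and name the variable or form that holds them. Remove the examples in 8.1 that cannot apply to this population.
- **Both arms:** unless Annexes 13 and 14 already have one, add one identical symptom-relapse item to the existing T1 and T2 telephone interviews. Word it so that patients who have not stopped can answer it, and without describing the intervention, so that the masking in 6.9 is kept. List it in Table 5 and report it by arm beside adverse drug events.

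Cost: protocol wording and one item in two questionnaires. At an assumed minute per call, this is 222 patients × 2 calls = 444 minutes, or about 7.4 hours of interviewing over the whole trial, within calls planned at 10 to 15 minutes each (6.7). No new contact is needed and no clinical rule changes.
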